#### 2.2.2. Attrition Management

Automated survey invitations will be configured in REDCap (Version 16.1.4) [42,43] to issue reminder notifications at 7 and 14 days for participants with incomplete follow-up surveys at T2 and T3. The ‘Save and Return later’ feature in REDCap will be enabled to enhance participant retention and reduce response burden by allowing surveys to be completed in multiple sittings. Incentives will only be offered upon completion of all questionnaires.

### 2.3. Measures

#### 2.3.1. Pathway Tool Acceptability and Feasibility Questionnaire

An author-developed survey will be used to evaluate the acceptability and feasibility of the Pathway Tool. The survey, adapted from the PEMAT (Patient Education Materials Assessment Tool) framework [47,48], will measure the ease of understanding, visual appeal, acceptability of language, readability, functionality, and ease of navigation of the Pathway Tool (intervention group only). See Section S4 of the Supplementary Materials for further details on this measure.

#### 2.3.2. Pathway Tool Engagement Metrics

Engagement metrics will be used to provide insights into how participants are using the Pathway Tool and guide improvements to make it more user-friendly. These metrics will be captured during participant use of the Pathway Tool. See Table 2 for engagement metrics and operational definitions.

#### 2.3.3. Parent Outcome Measures

Questionnaires developed by the authors will assess pre-to-post-intervention changes in (i) perceived self-efficacy in recognising and supporting flourishing in early childhood, (ii) perceived knowledge of how and when to seek support, and (iii) engagement with and participation in supports relevant to flourishing in the early years. These questionnaires will include items such as “I can tell when my child is doing well” and “I know about good programmes and services in my area that can help my child flourish”. The questionnaire items were developed by the research team and reviewed by experts in child wellbeing, child development, and questionnaire design. For further details, see Section S3 of the Supplementary Materials.

Parent wellbeing will be assessed pre- and post-intervention using the Mental Health Continuum–Short Form (MHC-SF) [49]. This scale measures three dimensions of mental health: emotional, psychological, and social wellbeing, and shows acceptable internal consistency (α = 0.89), test–retest reliability (0.65–0.70, *p* < 0.001), and low–moderate convergent validity in expected directions [50]. The Paediatric Quality of Life Inventory (version 4.0) (PedsQL 4.0) [51], which measures the health-related quality of life of children and adolescents, will be used for a health economics analysis. This analysis will quantify any improvements attributable to the Flourishing Intervention in terms of cost-effectiveness. This will enable the assessment of whether the intervention delivers meaningful improvements in child wellbeing relative to its costs, such as the incremental cost per improvement in quality-adjusted life years.

We do not anticipate significant improvements to parental wellbeing or paediatric quality of life within the timeframe of this study. Completion of these measures will be used to inform a future effectiveness trial.

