**Abstract:**

Background: Globally, rates of children with physical and mental health problems are increasing. Health issues in early childhood often persist into adulthood, highlighting the need to ensure children are supported to flourish from the start of life. Objectives: This protocol describes methods used to test the acceptability and feasibility of a novel digital Flourishing Intervention (designed to empower parents and promote child wellbeing), comprising a Flourishing Check (a newly developed online questionnaire) and a Pathway Tool (an online directory of high-quality, evidence-based programmes and resources). Methods: Using a randomised feasibility trial, participants (N = 600 parents of children aged 0–5 years) will complete the Flourishing Check. The intervention group (n = 400) will access the Flourishing Check and Pathway Tool, whereas a waitlist control group (n = 200) will access the Flourishing Check only. Results: The primary aim is to assess the acceptability and feasibility of the intervention through a mixed-methods design incorporating quantitative data from pre- and post-intervention questionnaires and qualitative data from focus groups. This will be assessed using a traffic light system, which will inform if and how to proceed to a future effectiveness trial. Secondary aims are to assess changes in parent and child outcomes. Primary outcomes will be assessed using descriptive statistics and thematic analysis. Secondary outcomes will be analysed using mixed-effects regression models. Conclusions: We anticipate that the Flourishing Intervention will be feasible and acceptable to parents. This trial is registered with the Australian New Zealand Clinical Trials Registry (ACTRN12626000187347).

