### 1.4. The Flourishing Intervention

In this protocol, we describe the Flourishing Intervention, designed to promote child flourishing by improving parents’ awareness of their children’s strengths and support needs, and their knowledge of when to seek support. This digital health intervention comprises a Flourishing Check and a Pathway Tool, conceptualised by the research team with the aim of providing parents with both knowledge of and access to timely supports. The design and testing of the Flourishing Intervention are nested within a longitudinal cohort study, ORIGINS, based in Perth, Western Australia. ORIGINS [35] is a collaboration between The Kids Research Institute Australia and Joondalup Health Campus, and is one of the most comprehensive studies of pregnant women and their families in Australia.

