## 2. Materials and Methods

### 2.1. Study Design

A randomised feasibility trial will be used to test the feasibility and acceptability of a new flourishing intervention and explore any areas for modification required (primary aim). A secondary aim will be to explore whether the intervention group shows any improvements in parent outcomes relative to controls after engaging with the Pathway Tool. This protocol is reported in accordance with SPIRIT guidelines and informed by the CONSORT extension for pilot and feasibility trials (see Section S2 of the Supplementary Materials) [40].

Participants will complete a screening form to determine eligibility and then be randomly allocated to either the intervention group (which will gain access the Pathway Tool immediately after completing the Flourishing Check), or the waitlist-control group (which will continue their usual activities and only gain access to the Pathway Tool after post-test assessments are completed or the final data collection time point has closed).

Quantitative and qualitative data will be collected at five timepoints: [T1] pre-intervention (baseline); [T2] acceptability and feasibility questionnaires (intervention group only), 1 week after T1; [T3] test–retest reliability (n = 200), 2–4 weeks after T1; [T4] qualitative feedback on the Flourishing Check and Pathway Tool (*n* ≈ 30, intervention group only), 3 months after T1; and [T5] post-intervention outcome measures, 6 months after T1. See Table 1 for a summary of the research procedure.

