## 3. Expected Results

We hypothesise that the Flourishing Intervention (Flourishing Check and Pathway Tool) will be acceptable and feasible to parents of children aged 0–5 years, as indicated by questionnaire responses and qualitative feedback (primary aim). Given the brief duration of the intervention and follow-up period, and the relative stability of many parenting and wellbeing characteristics over short timeframes, we anticipate detecting only small changes in most of the secondary outcome variables. We do not anticipate that we will detect significant improvements to parental wellbeing or paediatric quality of life within the timeframe of this study. However, this will be measured to assess the feasibility and sensitivity of these measures, and to inform effect size estimates and outcome selection for a future trial evaluating the intervention’s effectiveness.

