### 4.2. Outcomes of Research and Next Steps

If the Flourishing Child Intervention is assessed as acceptable and feasible by parents, it will provide accessible means for parents to gauge their child’s mental and physical health and engage targeted support when needed. The next phase of this project will test the effectiveness of the intervention in improving parent outcomes and early childhood flourishing. Insights gained through the feasibility trial will inform amendments to recruitment strategies, methods for maximising adherence and completion rates, data screening processes, and delivery of the intervention. Results from focus groups, questionnaires, and website metrics will inform refinements of the intervention itself to maximise utility and reduce participant burden.

Subsequent research will focus on implementing the intervention at scale in different geographical settings and with different population groups, initially in Western Australia. This will involve co-design with local consumers and contextual and cultural adaptation, ensuring acceptability and feasibility among different populations, including Culturally and Linguistically Diverse (CALD) families, Aboriginal and Torres Strait Islanders, families with neurodiverse children, and other groups [13]. In scaling up this digital intervention, the research team will contextualise the geographical region and local population, including digital access, literacy, and connectivity.

Future research will include a cost-effectiveness analysis comparing those who utilise the Pathway Tool and those who do not, as well as health service utilisation and associated costs. Project impacts will incorporate key recommendations to be articulated in a policy briefing paper. Findings will be disseminated widely through publications and stakeholder presentations.

Early childhood parenting interventions have tended to focus on reducing child problem behaviours [16,19,24]. The Flourishing Intervention is unique in its focus on enhancing the positive aspects of a child’s life. The Flourishing Intervention has the potential to increase parents’ awareness of their children’s strengths and support needs, and confidence in supporting them to flourish. According to the Logic Model provided in Figure 1, we anticipate the potential for long-term positive impacts as a result of parents engaging with the Flourishing Intervention (such as reduced incidence of mental health issues in children).

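### Both arms complete the Flourishing Check, so the between-group comparison estimates the Pathway Tool added to the Check, not the whole Flourishing Intervention as parts of the protocol claim

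*Protocol article*

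**What the plan says.** Section 1.4 defines the intervention by its two parts: "This digital health intervention comprises a Flourishing Check and a Pathway Tool". Section 3 repeats that definition.

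The Abstract says what controls receive: "a waitlist control group (n = 200) will access the Flourishing Check only". Section 2.2.1 has all participants complete the baseline battery. Table 1 marks the Check for both arms at T1, with a repeat at T3 for the test–retest work. Under section 2.1, controls "only gain access to the Pathway Tool after post-test assessments are completed or the final data collection time point has closed".

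On what the comparison measures, the text divides:

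- Section 2.1 frames the secondary aim as improvement relative to controls after use of the Pathway Tool. Section 2.6.2 ties between-group change to the Pathway Tool.
- Section 2.3.3 states: "This analysis will quantify any improvements attributable to the Flourishing Intervention in terms of cost-effectiveness". It gives an example of the metric: "such as the incremental cost per improvement in quality-adjusted life years".
- Section 3 says that parent wellbeing and paediatric quality of life are measured in part "to inform effect size estimates and outcome selection for a future trial" of the intervention's effectiveness.
- Section 4 describes the secondary aims as exploring the potential efficacy of the intervention.

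On the economics, section 4.2 says: "Future research will include a cost-effectiveness analysis comparing those who utilise the Pathway Tool and those who do not". It lists health service utilisation and its costs in the same sentence.

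**The concern.** A randomised comparison isolates only what differs between the arms. Here that is access to the Pathway Tool. The Check is a named component of the intervention and is meant to do something by itself: section 1.5 says it lets parents look at how their child is doing and points to domains where support may help. Section 2.2 provides support numbers in case completing it raises worries. It cannot be assumed inert.

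If the between-group difference is reported as the effect of the whole intervention, the result is attributed to a package that was never compared with its absence. Two uses are exposed. One is planning the effectiveness trial, for which section 3 wants effect sizes. The other is the economic statement in section 2.3.3, where the incremental benefit would be that of the Tool but the label would be that of the package. For the economics, a reader also cannot tell whether this trial or a later one carries the analysis.

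**Working it through.** **The plan's own figures.** Section 2.6.2 (Sample Size) gives 267 and 133 participants at follow-up and a detectable d of 0.30 at 80% power and alpha 0.05 (two-sided assumed).

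- Retention of two thirds: 400 × 2/3 = 266.7 and 200 × 2/3 = 133.3, which agree.
- Detectable d = (1.960 + 0.842) × √(1/133 + 1/267) = 2.802 × 0.1061 = 0.297. Allowing for the Mann–Whitney efficiency of 3/π, 0.297 / √0.955 = 0.304.
- Power at d = 0.30 is 80.7% by the normal approximation and 78.9% with the Mann–Whitney allowance.

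The figures reproduce and are not in dispute. The 0.30 is the detectable difference between these two arms, so it already refers to the Tool added to the Check.

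**What the contrast identifies.** For a given outcome from T1 to T5, write:

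- S = change that would occur anyway over six months;
- C = effect of completing the Check without the Tool;
- T = further effect of being offered the Tool once the Check is completed, including the tailoring of recommendations to Check responses (sections 1.6 and 2.4).

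| Quantity | Expression |
|---|---|
| Expected change, control | S + C |
| Expected change, intervention | S + C + T |
| Between-group difference | (S + C + T) − (S + C) = T |
| Effect of the whole intervention | C + T |

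The trial estimates T. The whole-intervention effect needs C as well. Within-group change does not supply it: the control change is S + C, and with no arm free of the Check the two terms cannot be separated.

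**Size of the gap.** The gap is C, for which the documents give no value. If C is zero, the two effects coincide. If C is positive, T understates the whole. If C is negative, for example because the Check raises worry or makes parents rate themselves more critically, T overstates it. Neither the size nor the sign can be fixed from the text.

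**The sections side by side.**

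| Section | Effect named | Supported by the design? |
|---|---|---|
| 2.1, 2.6.2 | Pathway Tool | Yes |
| 2.3.3 | Whole intervention, as cost-effectiveness | No |
| 3 | Effect sizes for a trial of the intervention | Only if that trial's control also gets the Check |
| 4 | Efficacy of the intervention | No |

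**The economic analysis.** Section 2.3.3 describes a health economics analysis using PedsQL, with incremental cost per QALY as an example, and labels the benefit as that of the whole intervention. Section 4.2 assigns a cost-effectiveness analysis to future research and organises it around use of the Pathway Tool. The two sections differ on which study carries the analysis and on what is compared.

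**The case against.** The strongest reply is that the analysis is already right where it matters. Sections 2.1 and 2.6.2 name the Pathway Tool as the source of any between-group difference, the Abstract is open about what controls receive, and these comparisons are declared exploratory. No model or sample size needs to change. That stands, and it makes this an internal contradiction rather than a wrong analysis.

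Three stronger readings are tempting, and the documents do not support them.

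- *The Check drops out of the comparison altogether.* It does not. Check responses steer what the Tool recommends, so that joint contribution stays within T. Only the effect of the Check without the Tool is lost.
- *The future trial will be mis-sized by a calculable factor.* Any factor would need an assumed share for the Check and would have to treat d = 0.30 as the whole-intervention effect, which it is not. The protocol also does not say that the future control will go without the Check. Whether there is any mis-sizing depends on that choice.
- *No costs are collected, so the economic analysis cannot be delivered.* Table 1 schedules participant assessments, and delivery costs may come from project records. Section S3 is not shown, and section 4.1.2 says the parenting items include questions on engagement with specific programmes. Costing detail may also sit in a fuller document. Nor does section 4.2 say outright that no economic analysis happens here, so the conflict with section 2.3.3 is a tension and not a flat contradiction.

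**Conclusion.** The point holds as a mismatch between design and claim. The comparison estimates the effect of offering the Pathway Tool in addition to the Flourishing Check. The whole-intervention attribution in section 2.3.3, the effect-size use in section 3 and the efficacy wording in section 4 go beyond that. The conclusion rests on the protocol's own definition of the intervention and on both arms completing the Check; it needs no assumption about how strong the Check is. The discrepancy has no numerical size because the stand-alone effect of the Check is unknown and cannot be estimated here. The primary acceptability and feasibility aims and the sample size are unaffected. Separately, sections 2.3.3 and 4.2 need to agree on which study carries the cost-effectiveness analysis.

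**What to change.** 1. In sections 2.3.3, 3 and 4, replace attribution to the whole intervention with *the Pathway Tool in addition to the Flourishing Check* wherever the claim rests on the between-group comparison.
2. In section 3, add that the effect-size estimates carry over only to a future trial whose control group also receives the Check.
3. Reconcile section 2.3.3 with section 4.2 in one of two ways. Either defer the cost-effectiveness and QALY statement to the later study and keep PedsQL here as an outcome and completion measure, or keep it here as an incremental Pathway Tool comparison, naming the source of the costs and how PedsQL scores yield QALYs.

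Items 1 and 2, and deferral under item 3, are wording changes with no effect on randomisation, data collection or sample size. Keeping the economic analysis means documenting its cost and utility inputs. The downside is a narrower claim: the trial can speak to the added value of the Tool, not of the full package.

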#### 2.3.4. Focus Groups

A subset of participants (approximately n = 30) will participate across two focus groups to report on how they used the Pathway Tool and their experiences and engagement with the supports. Focus group questions have been developed in collaboration with members of The Flourishing Child Consumer and Community Advisory Group. To achieve saturation, we will follow procedures recommended by Krueger and Casey [49]. They advise recruiting smaller groups of five to eight participants in focus groups when dealing with topics that may be sensitive and/or are experienced by the participants. Usually, saturation is achieved after completing three to four groups. We will conduct two focus groups before reviewing responses to assess whether the questions are eliciting responses that are relevant to our aims. We will then amend questions if required and conduct two more focus groups. We will recruit five to eight participants into each group. We will stratify those who register by demographics and other factors (e.g., parents of children with additional challenges) and invite them to participate in either online or in-person focus groups.

All focus group participants will receive an e-gift voucher of $50 for their contribution. Focus groups will be recorded and audio-transcribed. Qualitative data collected during focus groups will be analysed to identify key themes regarding programme engagement, acceptability, and confidence in accessing support and resources.

### 2.4. Data Collection and Management

Study data will be collected and managed using REDCap electronic data capture tools hosted at The Kids Research Institute Australia [43]. REDCap (Research Electronic Data Capture) is a secure, web-based software platform designed to support data capture for research studies, providing (1) an intuitive interface for validated data capture, (2) audit trails for tracking data manipulation and export procedures, (3) automated export procedures for seamless data downloads to common statistical packages, and (4) procedures for data integration and interoperability with external sources. Participants will be issued a unique identifier, and all data will be deidentified. When participants complete T1 data collection in REDCap, their Flourishing Check results, child’s date of birth, and sex data will be synced to the data platform hosted within an Amazon Web Services account owned by ORIGINS. This will enable Flourishing Check results to inform which resources are recommended by the Pathway Tool. The Pathway Tool will link to the data platform only (there will be no direct connection to REDCap). A data management committee (DMC) will not be established, and no interim analysis or formal stopping rules are planned for this trial due to its low risk and short duration. Any adverse events associated with this research will be reported to UWA HREC according to standard procedures.

### 2.5. Data Screening

Data screening will be automated using formulae within REDCap’s data quality functionality. Participant records will be flagged where responses are inconsistent or contradictory, attention checks are failed, or key variables are missing responses. As an additional measure, records will be manually screened by members of the research team to validate participants. Data will be monitored by research team members throughout the recruitment and follow-up periods to ensure that (1) recruitment targets are achieved, (2) participants are reimbursed appropriately and efficiently, and (3) only valid data is included in the analysis.

### 2.6. Data Analysis

#### 2.6.1. Primary Outcomes

Acceptability and Feasibility:

The acceptability and feasibility of the Flourishing Check and Pathway Tool will be assessed using a convergent mixed-methods design [52] involving data from questionnaires and focus groups. Additional themes emerging from focus groups, as well as website engagement metrics, will inform future modifications to these tools. Convergent or concurrent mixed methods (also called “parallel”) projects gather quantitative and qualitative data separately, or parallel to each other, and analyse them together. All quantitative and qualitative data will be triangulated and compared for consistency, validity, and credibility. The results will be synthesised to identify themes and recommendations for improving the intervention. Table 3 provides a summary of the data triangulation process and criteria to meet different levels of feasibility and acceptability. This has been created based on the ADePT framework, where 3 categories (green, amber, or red) are used to assess whether a study should progress from a pilot to an efficacy trial [53].

Questionnaires:

The author-developed questionnaires will assess the ease of use, understanding, visual appeal, acceptability of language, readability, functionality, and ease of navigation of the Flourishing Check and Pathway Tool, with higher scores operationalised as greater acceptance. These data will be analysed using descriptive statistics. Additionally, responses to open-ended questions will be subjected to thematic analysis according to best practice, described below [54].

Focus Groups:

Focus groups will be used to assess the feasibility and acceptability of the Pathway Tool. Using the approach of Braun and Clarke [54] for thematic analysis, transcripts will be iteratively coded, and codes will be collated into higher-level themes. Transcripts will be reviewed to identify all instances of thematic codes, with codes expanded or collapsed as required. Qualitative data will be analysed using qualitative content analysis [55], assigning a code to each concept using NVivo 14. Similar concepts will be identified and categorised into categories. Data will be analysed using a phenomenological approach (i.e., as a description of experiences as consciously experienced by participants), and narrative themes will be deducted until saturation. The coding process will be guided by the following deductive constructs: intervention acceptability, engagement, and application; mental health and wellbeing experiences; and suggestions for programme revisions.

Engagement metrics:

This data will be used for exploratory purposes to understand how users interact with suggested resources. Exploratory engagement (e.g., clicking resources within the tool or following external links) will indicate whether recommendations are perceived as relevant and worth investigating, supporting acceptability. Recurring engagement, such as saving resources, will indicate sustained interest and practical feasibility of repeated use over time. Collaborative engagement (i.e., copying links to share with others) will further signal acceptability by indicating that users value the content enough to recommend it within their community. These metrics will inform future modifications to the Pathway Tool if the feasibility or acceptability receives an ‘amber’ outcome (see Table 3).

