Lastly, the Consumer and Community Advisory Committee strongly agreed that enforcing user registration may create a barrier to engagement with online content. Therefore, participants will not have to create a user account to engage with the Pathway Tool. This limits our ability to control who accesses the tool, as anyone who receives the URL can access it. Therefore, engagement metrics may be inflated by users who are not verified, participants. Additionally, control participants may gain access to the tool during the study. This will be partly mitigated by the URL being hidden from searches. Given the low-risk nature of the intervention and the study context, more intensive monitoring approaches (e.g., individual-level tracking, mandatory logins, or detailed analytics linkage) were considered disproportionate to the aims of the study and not feasible within available resources. Importantly, such approaches would also introduce additional privacy considerations and participant burden, which may further impact participation and engagement. Future research could implement stricter controls to more accurately assess the efficacy of the Pathway Tool.

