**ASSESSMENTS**:								
Demographics			X					
Flourishing Check Acceptability and Feasibility Questionnaire ^†^			X					
Pathway Tool Acceptability and Feasibility Questionnaire ^×^*				X				
Focus groups *						X		
Perceived self-efficacy in recognising and supporting flourishing in early childhood ^×^			X				X	
Perceived knowledge of how and when to seek support ^×^			X				X	
Engagement with and participation in supports relevant to flourishing in the early years ^×^			X				X	
Mental Health Continuum–Short Form (MHC-SF)			X				X	
Paediatric Quality of Life (PedsQL)			X				X	

* Only the intervention group will complete these assessments. ^×^ Can be found in Section S3 and S4 of the Supplementary Materials. ^†^ Can be found in Section S5 of the Supplementary Materials. The analysis plan and results pertaining to these measures (i.e., test–retest reliability measured at T3 and Flourishing Check Acceptability and Feasibility Questionnaire measured at T1) will be detailed in a separate paper explaining the development of the Flourishing Check.

**Table 2 children-13-00581-t002:** Description of Pathway tool engagement metrics.

Engagement Type	Engagement Category	Metric	Description
Passive Information Access	Exploratory Engagement	Level 1–A resource clicked within the Pathway Tool Level 2–Participant follows link to external resource	An indicator over two levels that the participant finds the resource engaging and relevant
Active Information Access	Recurring Engagement	Total number of resources saved	An indicator that participant is interested in engaging with the resource more than once
Community Participation	Collaborative Engagement	A resource link copied to share	An indicator that the participant wants others in the community to engage with the resource

**Table 3 children-13-00581-t003:** Data triangulation process and criteria used to assess feasibility and acceptability.

	Red (Do Not Proceed to Full-Scale RCT)	Amber (Consider Proceeding to Full-Scale Trial Only After Intervention and Protocols Have Been Refined)	Green (Proceed to Full-Scale RCT Without Refinement)

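### The click metric in Table 2 does not separate recommended from other resources, so on its own it cannot support the planned conclusion about how recommendations are perceived

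*Protocol article*

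**What the plan says.** Section 2.3.2 refers to Table 2 for the engagement metrics and their operational definitions. In Table 2 exploratory engagement is measured as "Level 1–A resource clicked within the Pathway Tool Level 2–Participant follows link to external resource", and described as "An indicator over two levels that the participant finds the resource engaging and relevant". The object of that description is the resource; recommendations are not mentioned.

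Section 2.6.1 introduces the metrics as exploratory and as a way to see how users deal with resources suggested to them. It then interprets them: "Exploratory engagement (e.g., clicking resources within the tool or following external links") "will indicate whether recommendations are perceived as relevant and worth investigating, supporting acceptability". The same paragraph says the metrics will inform changes to the tool after an amber outcome. Section 2.6.3 adds that they give a more objective view of use when the questionnaire and focus-group findings disagree.

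Three other places bear on the point:
- The Abstract describes the Pathway Tool as "an online directory of high-quality, evidence-based programmes and resources".
- Section 2.4 says of the transfer of T1 data to the data platform: "This will enable Flourishing Check results to inform which resources are recommended by the Pathway Tool".
- Section 4.1.2 says no account is required and "anyone who receives the URL can access it". It rejects individual tracking, compulsory logins and detailed linkage of analytics as out of proportion to the study's aims.

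**The concern.** The conclusion concerns recommendations; the measurement concerns resources in general. Recommendations are the part of the directory selected for a parent by the child's Flourishing Check result. A parent who ignores that selection and browses elsewhere adds to the count in the same way as a parent who follows it. So may a visitor who arrives with the URL and has no Check result.

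What is at stake is the tailoring, which links the Flourishing Check to the Pathway Tool. If clicks were plentiful but mostly on other content, the report could still say that the recommendations were seen as relevant. After an amber result, the team would then lack the figure showing whether the tailoring needs work. The questionnaire domains named in Sections 2.3.1 and 2.6.1 cover matters such as understanding, appearance, language, functionality and navigation, and do not list relevance of recommendations. As far as the article shows, clicks are therefore the only quantitative source named for that question. The item lists in the supplement are not shown.

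**Working it through.** The plan gives no figure for these metrics, so there is none to reproduce. The check compares the definition with the inference and then illustrates the gap.

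**Definition against inference**

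| Element | Needed for a statement about recommendations | Given in Table 2 |
|---|---|---|
| Event counted | Click or external follow on a recommended resource | Click or external follow on any resource |
| Comparison | The same for resources not recommended | None |
| Denominator | Number of times each kind was displayed | None |

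The two kinds of content differ, because the selection depends on the Check result (Sections 1.6 and 2.4) while the tool as a whole is a directory (Abstract). The article describes no means of recovering the split later, since Section 4.1.2 rules out individual tracking and detailed linkage.

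**Bounds from the definition alone.** Ten clicks all on recommended resources and ten clicks all on other resources both score 10 at Level 1. For any total, the recommended share is unconstrained between 0% and 100%.

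**Illustration (all values assumed).** Let *s* be the share of displays that are recommendations, and *w* the click rate per display of a recommended resource relative to another. The share of clicks on recommended resources is

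*s·w* / (*s·w* + 1 − *s*).

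- *s* = 0.25, *w* = 1 (recommendation makes no difference): 0.25 / (0.25 + 0.75) = 0.25, or 250 of 1,000 clicks.
- *s* = 0.25, *w* = 3: 0.75 / (0.75 + 0.75) = 0.50, or 500 of 1,000 clicks.

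Table 2 would report 1,000 in both cases. The total is held equal on purpose, to show that it can be.

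**Would a flag with displays recover the difference?** Divide clicks by the display share in each class and take the ratio:

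- First case: (250 / 0.25) / (750 / 0.75) = 1,000 / 1,000 = 1.
- Second case: (500 / 0.25) / (500 / 0.75) = 2,000 / 666.7 = 3.

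The display count is needed as well as the flag. If recommendations made up half of what was shown (*s* = 0.50), 500 of 1,000 clicks would give (500 / 0.50) / (500 / 0.50) = 1, which is no preference at all.

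**The case against.** **The scope sentence.** Section 2.6.1 opens by referring to suggested resources, so the clicks that follow could be read as clicks on those only. This shows which question the authors want answered. It does not restrict the metric: neither the next sentence nor Table 2 carries the limit, and Table 2 is where Section 2.3.2 sends the reader for definitions.

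**Condensed article.** Logging detail may sit in a document not shown. Section S1 of the supplement, for instance, is cited for the tool's development. That is possible. But the article prints both the definition and the interpretation, and the two do not match; the point does not depend on a missing detail.

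**Display of content.** The article does not say how resources are laid out or what a visitor without a Check result sees. That such visitors receive no recommendation is a reasonable inference, but it is not stated. The mismatch would remain if every click came from a verified participant.

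**Total clicks.** If recommendations attract clicks, the total should rise, so it is not empty of information, and very low clicking would count against the recommendations. This stands. But the control group has no planned access before follow-up closes, and no group uses an untailored version, so a high total has no comparator from which to attribute it to the recommendations.

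**Consequences.** A reader might infer that poor tailoring would go undetected, or that the decision to proceed is compromised. The article supports neither. Focus groups ask how parents used the tool, their coding includes suggestions for revision, and open-ended answers are analysed thematically. Table 3 rests on questionnaire ratings and focus-group themes, with no click threshold.

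**Conclusion.** The concern holds in a limited form. As defined, the exploratory engagement metric cannot distinguish interest in recommended resources from general browsing, so it cannot by itself support the sentence on perceived relevance of recommendations. The size of the ambiguity is complete with respect to the split (0% to 100% for a given total). The consequence is minor to moderate: the metrics are exploratory and do not enter the red/amber/green criteria, but they steer modifications after an amber result and are consulted when other data diverge.

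It would go too far to say that clicks carry no information, or that followed and ignored recommendations must give equal counts. They can give equal counts, which is enough to defeat the inference. The conclusion assumes that the tool lets users open content beyond their own recommendations, as its description as a directory implies, and that no unseen supplement already defines a recommended flag. The 25% display share and threefold rate are illustrative only.

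**What to change.** In Table 2, record with each click and external follow an anonymous event-level flag for whether that resource was displayed as a recommendation, and count displays of both kinds. Report clicks over displays for recommended and for other resources, and base the sentence on relevance in Section 2.6.1 on that contrast.

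Because the tool itself uses the Check results to choose what it recommends (Section 2.4), the flag should need neither a login nor linkage to individuals, and so should be compatible with Section 4.1.2. The article does not describe the tool's technical set-up, so this should be confirmed with the developers.

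If the flag cannot be logged within that privacy position, restrict the sentence in Section 2.6.1 to general interest in the tool's content and leave relevance of recommendations to the focus groups and open-ended answers.

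The first option costs a small change to event tagging before launch and one more descriptive table. The second costs only a change of wording, but gives up the quantitative answer.
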